#### 2.5.2. Quantitative Data Collection Teachers

Quantitative implementation data from teachers will be collected using two structured questionnaires at two timepoints, baseline (pre-intervention/before the delivery of the sessions) and follow-up (post-intervention/after the delivery of the two sessions) (Table 5). The first questionnaire will be the teacher self-assessment questionnaire, and it will be completed by the trained teachers. This questionnaire will include 20 items evaluating preparation, familiarity with the intervention, alignment with school values, feasibility, confidence, and resource needs. Moreover, it will use open questions regarding student engagement, and the quality of Personal Plan implementation. For both questionnaires, teachers will rate their agreement on a four-point Likert scale, ranging from 1 (disagree) to 4 (agree).

#### 2.5.3. Qualitative Data Collection for Teachers, MTs, and Students

Qualitative data from students (Table 4), MTs, and teachers (Table 5) will be collected through semi-structured interviews, focus groups and open-ended written questions, post-intervention. Following the intervention, MTs will organize semi-structured interviews or focus groups, inviting participation from students and teachers (at least 3–4 students and 2–3 teachers from each school), separately. These interviews/focus groups will explore the perceived effectiveness, cultural relevance of intervention, ease of understanding, and areas for improvement. Regarding the MTs, a FRESHAIR4Life team member will interview them in a semi-structured format about their experience organizing the intervention, any difficulties they encountered, and suggestions for improvement in future implementations.

### 2.6. Sample Size

A sample size calculation was conducted using G*Power software (version 3.1) for the most complex analysis planned in this study, multiple linear regression examining the relationship between tobacco-related behaviors (initiation, use, and susceptibility) and key predictors (adolescent attitudes and perceptions about smoking) [48,49]. For a medium effect size (f^2^ = 0.15), an alpha level of 0.05, and a desired power of 0.80, the analysis indicated that a minimum of 77 participants would be required. Taking into account a potential 20% attrition rate and considering that the most complex analysis requires a sample size of 77 participants, the minimum target sample size was set at 93 participants; however, we expect that at least 450 adolescents will participate in our study.

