The aforementioned findings have important implications for smoking prevention programs in Greece and highlight the need for further exploration of tobacco control interventions in Greek schools. Therefore, the aim of this study protocol is to describe the cultural adaptation procedure and the proposed implementation and evaluation of the school-based “Implementation Intentions” program aimed at reducing TU susceptibility among Greek adolescents aged 13–16 in school settings. The specific research questions of this study are:To what extent is the Greek adaptation of the INTENT program associated with changes in tobacco use susceptibility and related attitudes among adolescents aged 13–16?How do key stakeholders, including teachers and a representative group of adolescents, perceive the feasibility, acceptability, and potential effectiveness of the INTENT program?”

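### The minimum target of 93 does not leave 77 students after 20% attrition; the inflated figure should be 97

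*Protocol article*

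**What the plan says.** Section 2.6 of the protocol article opens: "A sample size calculation was conducted using G*Power software (version 3.1) for the most complex analysis planned in this study". It describes that analysis as "multiple linear regression examining the relationship between tobacco-related behaviors (initiation, use, and susceptibility) and key predictors (adolescent attitudes and perceptions about smoking"). The inputs are given as follows: "For a medium effect size (f^2^ = 0.15), an alpha level of 0.05, and a desired power of 0.80". The result is that "the analysis indicated that a minimum of 77 participants would be required". The allowance for loss is introduced with "Taking into account a potential 20% attrition rate", and the sentence goes on that the most complex analysis "requires a sample size of 77 participants, the minimum target sample size was set at 93 participants". The same sentence then says that at least 450 adolescents are expected; section 2.2 anticipates about 480.

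Research question 1, at the end of the Introduction, asks how far the adapted program is "associated with changes in tobacco use susceptibility and related attitudes among adolescents". Section 2.7 evaluates changes with paired t-tests and regression. It calls the study exploratory and takes effect sizes with 95% confidence intervals as the primary indicators.

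**The concern.** A minimum target that allows for attrition should leave the required number once the stated fraction has been lost. The 77 and the 20% are both in section 2.6, and 93 does not follow from them. A reader who takes the section at face value would believe that 93 enrolled students protect the stated 80% power against a 20% loss, and they do not. What is at stake is the correctness of a published sample-size figure. The feasibility of the study is not in question.

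A secondary matter is that the only power figure belongs to a regression of tobacco-related behaviors on attitudes and perceptions. As described, that model does not test the mean change from baseline to follow-up that research question 1 is about.

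**Working it through.** **Inputs.** From section 2.6: f² = 0.15, alpha = 0.05, power = 0.80, 77 required, 20% attrition, minimum target 93, at least 450 expected. The number of predictors is not given in the article and is inferred below.

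**Step 1: reproduce 77.** For the overall F-test in multiple linear regression with k predictors, the noncentrality is λ = f² × N, with k and N − k − 1 degrees of freedom. The smallest N with at least 80% power is:

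| k | N |
|---|---|
| 2 | 68 |
| 3 | 77 |
| 4 | 85 |
| 5 | 92 |

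Three predictors give exactly 77 (power 0.802). The 77 therefore reproduces.

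**Step 2: reproduce 93.**
- Multiplying by 1 + attrition: 77 × 1.20 = 92.4, rounded up to 93. This is the plan's figure.
- Dividing by 1 − attrition: 77 / (1 − 0.20) = 96.25, rounded up to 97.

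**Step 3: check both targets against a 20% loss.**
- 93 × 0.80 = 74.4, so 74 completers, three short of 77.
- 97 × 0.80 = 77.6, so 77 completers.
- Put differently, 93 tolerates a loss of only (93 − 77) / 93 = 17.2%.

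**Step 4: power at 74 completers.** With k = 3 and λ = 0.15 × 74 = 11.1, power is 0.783, against 0.802 at 77. The shortfall is about 2 percentage points.

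**Step 5: expected enrollment.** 450 × 0.80 = 360 completers, more than four times 77.

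**Step 6 (for the optional addition): detectable pre-post change.** This uses a paired t-test with two-sided alpha 0.05 and 80% power. The change is expressed in standard deviations of the within-student change. With 360 independent pairs, the detectable change is 0.148, about 0.15.

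For clustering by class, the design effect is 1 + (m − 1) × ICC. I assume m = 15 evaluated students per class: 480 students at about 20 per class is 24 classes, and 360 / 24 = 15. The ICC of the change is not in the document; 0.02 to 0.10 is an assumed range.

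| ICC (assumed) | Design effect | Effective pairs | Detectable change | 95% CI half-width |
|---|---|---|---|---|
| 0 | 1.00 | 360 | 0.15 | 0.10 |
| 0.02 | 1.28 | 281 | 0.17 | 0.12 |
| 0.05 | 1.70 | 212 | 0.19 | 0.14 |
| 0.10 | 2.40 | 150 | 0.23 | 0.16 |

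The half-width is t(0.975) / √(effective pairs), in the same units.

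**The case against.** The strongest reply is that nothing turns on the error. The sentence that sets 93 also expects at least 450 students, and 360 completers far exceed both 77 and 97. Even at the stated minimum the loss of power is about 2 points. All of this stands, and it limits the weight of the point. It does not make 93 correct: the figure is presented as the minimum and is inconsistent with the two numbers beside it.

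On the choice of analysis, the reply is that sizing a pilot on its most complex model is a disclosed choice. Susceptibility is among the regression outcomes, section 2.7 lists regression among the methods for evaluating change, and the study is exploratory with estimation as its primary reading. This largely stands. The regression as described still does not test a mean change, but the article makes no power claim for that change, so none is wrong.

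Three stronger readings are tempting, and the document does not support them.
- A reader might infer that 93 students are too few to evaluate the program. The document gives no target change and no standard deviation of change, so this cannot be shown. At 74 independent pairs the paired test detects a change of 0.33 with 80% power; whether that is adequate depends on a target that is not stated.
- A reader might carry a design effect of 1.7 (ICC 0.05, 15 per class) over to 74 completers. Spread over about 24 classes, 74 completers are about 3 per class, and at the same ICC the design effect is 1 + (74/24 − 1) × 0.05 = 1.10.
- A reader might count the unstated number of predictors as an error. It is a detail that an article commonly leaves to the full protocol, and 77 reproduces exactly with three.

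**Conclusion.** The minimum target is wrong as written. It inflates 77 by multiplication where division by the retained fraction is needed, and it falls four short of the correct 97. The arithmetic rests only on figures in section 2.6. The power figure of about 78% at 74 completers also rests on three predictors, inferred because that number reproduces 77, and on independent students. The practical effect is small because the expected enrollment is far above either number.

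The mismatch between the powered regression and research question 1 is accurate as a description, but it is not an error in a stated figure. A precision statement for that question would be useful and remains optional. Its clustered values rest on the assumed ICC range and class size.

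**What to change.** In section 2.6, replace 93 with 97 and show the step: 77 / (1 − 0.20) = 96.25, rounded up. This changes one number and needs no extra recruitment, no design change and no change to the analysis.

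Optionally, add one or two sentences for research question 1. With about 360 pairs (450 less 20%), a standardized pre-post change of about 0.15 is detectable with 80% power if students are independent. Under class clustering the figure is about 0.17 to 0.23, for an assumed ICC of 0.02 to 0.10 with 15 students per class. The matching 95% CI half-widths, about 0.10 for independent students and 0.12 to 0.16 under clustering, would suit the article's emphasis on effect sizes and intervals.

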### 2.7. Data Analysis

Quantitative data will be analyzed using the IBM SPSS 29 program. Descriptive statistics will summarize participant characteristics and engagement metrics. Paired *t*-tests and regression analyses will evaluate changes in the tobacco-related behaviors and attitudes of the participating students. Multiple linear regression analysis will be used to assess the strength and direction of the relationships between variables across the implementation period. As this study is exploratory, *p*-values will be interpreted alongside effect sizes and 95% confidence intervals. These will be the primary indicators of the strength and precision of the potential associations found. Specifically, Cohen’s d will be reported for paired *t*-tests, and standardized beta coefficients (β) for regression analyses. Statistical significance will be set to *p* < 0.05.

Interviews/focus groups will be audio-recorded, transcribed, and analyzed thematically by the MTs. More specifically, qualitative data will be analyzed using Braun and Clarke’s six-step framework for thematic analysis (Braun and Clarke) [50]. This involves transcribing and thematically analyzing the interviews and focus groups. First, the process involves verbatim transcription of audio-recorded interviews and focus groups, followed by multiple readings to understand the content. The transcripts will then be coded inductively (allowing themes to emerge) and deductively (focusing on study-specific aspects like adherence and quality of life). Codes will be grouped into categories, then refined into broader themes and subthemes. Finally, these themes will be presented with supporting quotes, and the qualitative findings will be triangulated with quantitative data to identify convergence or divergence between measurable outcomes and self-reported experiences [51].

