### 2.2. Study Population

The participants in this study will be categorized into three groups: the MTs, the teachers and the adolescents. Firstly, a selected group of three experienced educators/trainers who will act as MTs will be recruited. These individuals will be responsible for training the school teachers and overseeing the fidelity of the intervention delivery. MTs will undergo training sessions on tobacco prevention, facilitation techniques, and the “If–Then” planning methodology. Based on their new knowledge and skills, MTs will conduct training sessions and provide feedback and support to teachers throughout the implementation phase. Secondly, school teachers will be selected to participate in the intervention. These teachers will be trained by the MTs to deliver the tobacco prevention intervention to the adolescent participants. All teachers from the participating schools (approximately n = 250) will be invited to participate in the program. However, as this is a pilot intervention, the first four to five teachers from each school will be accepted to participate in the study, resulting in a total of 20 to 25 participants. The first-come, first-served approach was primarily adopted for pragmatic reasons, aligning with the goals of a pilot implementation study. Firstly, as this is an initial feasibility and implementation protocol, the main objective is to determine if the intervention can be successfully delivered by willing teachers in a real-world setting, rather than to recruit a perfectly representative sample. Secondly, restricting participation to 4–5 teachers per school creates a practical and manageable group size for the intensive training provided. Nevertheless, and considering that each classroom includes around 20 students, we anticipate that the intervention will reach approximately 480 adolescents.

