#### 2.4.2. Implementation Phase of the Study—Teachers Utilizing the Intervention at Their Classrooms (Phase IV)

The second phase of the intervention will be based on the deliverance of the “Implementation Intentions” intervention by the teachers at the schools. The implementation, as mentioned above, will be conducted in six different schools and will consist of two structured sessions (Table 3). Both sessions, each lasting two school hours (~90 min), will be delivered by trained teachers, scheduled approximately two months apart. MTs will oversee all sessions and assist teachers where needed. In the first session, teachers will introduce our intervention to students. Introducing our intervention, teachers will explain that through this program students will have the opportunity to explore the factors in their life that may influence them to smoke. Teachers will highlight the fact that committing to do something by putting this commitment down on paper is much more likely to result in success, by creating a “Personal Plan (PP)”. This session includes interactive conversations with students addressing myths and truths about TU and the long-term effects of initiating smoking, as well as quizzes regarding TU. The first session will conclude with a written exercise outlining each student’s refusal tactics, followed by the development of their Personal Plans (PPs). The second session aims to strengthen students’ personal resilience and highlight the complexity of external influences on their decision to remain smoke-free. Moreover, teachers will examine what students can recall from the previous lecture. Students will be informed about how smoking interplays with stress and once again, they will create their PP. It should be noted that both quantitative and qualitative data will be collected by the MTs, before, during and after the intervention.

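### Student-level paired t-tests ignore class-level variation in pre-post change, so the 95% CIs that Section 2.7 makes primary are probably too narrow for inference beyond these classes

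*Protocol article*

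**What the plan says.** Three parts of the protocol article bear on this.

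- **Analysis.** Section 2.7 states that paired t-tests and "regression analyses will evaluate changes in the tobacco-related behaviors and attitudes of the participating students". It adds: "Multiple linear regression analysis will be used to assess the strength and direction of the relationships between variables across the implementation period". Because the study is exploratory, p-values are to be "interpreted alongside effect sizes and 95% confidence intervals. These will be the primary indicators of the strength and precision of the potential associations found". The next sentences name Cohen's d for the paired t-tests, standardized betas for the regressions, and a 0.05 threshold. The primary indicators therefore include the pre-post comparison as well as the regressions.
- **Delivery.** Under Section 2.2.3, students enter as members of the trained teachers' classes. Section 2.2 takes four to five teachers per school and says: "considering that each classroom includes around 20 students, we anticipate that the intervention will reach approximately 480 adolescents". Section 2.4.2 says that both sessions "will be delivered by trained teachers, scheduled approximately two months apart". Section 2.1 fixes six schools.
- **Sample size.** For a regression with f² = 0.15, "an alpha level of 0.05, and a desired power of 0.80", Section 2.6 reports that "the analysis indicated that a minimum of 77 participants would be required".

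No section mentions correlation within class, teacher or school, an ICC, a design effect, a mixed model, GEE or cluster-robust errors. Section 3.1 does expect delivery to vary with the teacher's smoking status, workload and motivation.

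**The concern.** A paired t-test treats the students' change scores as independent. Pairing removes stable differences between students and between classes. It does not remove differences between classes in how much they change, and teacher-dependent delivery, which Section 3.1 anticipates, produces exactly those. Students who share a teacher, a session and a peer group then carry partly the same information about the mean change.

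The standard error of the mean change is what suffers, and it determines the interval that Section 2.7 names as primary evidence. The first research question asks how far the adapted program is associated with change in susceptibility, and with no control group the pre-post change is the main quantitative answer. An interval that is too narrow could present class or teacher variation as a change that other classes should expect.

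An analysis plan not shown here cannot be assumed to settle this, because the article itself names the methods.

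**Working it through.** **The plan's own figure.** Overall F test in multiple regression, noncentrality f²·N, df k and N − k − 1. The article does not state the number of predictors k. With k = 2, 3, 4 and 5, the required N is 68, 77, 85 and 92. So k = 3 reproduces 77 exactly (power 0.802), for independent observations and with no allowance for clustering.

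**Inputs.**
- About 480 students at 20 per class (Section 2.2): 480/20 = 24 classes, or 4 per school. This count is inferred. The article says 20 to 25 teachers, while 4 to 5 in each of six schools is 24 to 30.
- With 450 students and 20% attrition (Section 2.6): 450 × 0.8/24 = 15 pairs per class.
- Class ICC of the change score: not given. Assumed range 0.01 to 0.10.

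**Mean change.** With m pairs per class, DE = 1 + (m − 1)·ICC. The correct interval is √DE times as wide, effective N = 24m/DE, and type I error = 2·[1 − Φ(1.96/√DE)]. The last column is a simulation of the paired t-test with no true change (24 equal classes, 40,000 runs).

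| m | ICC | DE | √DE | Effective N | Type I, formula | Type I, simulated |
|---|---|---|---|---|---|---|
| 15 | 0.01 | 1.14 | 1.07 | 316 | 6.6% | 6.7% |
| 15 | 0.02 | 1.28 | 1.13 | 281 | 8.3% | 8.5% |
| 15 | 0.05 | 1.70 | 1.30 | 212 | 13.3% | 13.6% |
| 15 | 0.10 | 2.40 | 1.55 | 150 | 20.6% | 20.5% |
| 20 | 0.01 | 1.19 | 1.09 | 403 | 7.2% | 7.2% |
| 20 | 0.02 | 1.38 | 1.17 | 348 | 9.5% | 9.4% |
| 20 | 0.05 | 1.95 | 1.40 | 246 | 16.0% | 15.7% |
| 20 | 0.10 | 2.90 | 1.70 | 166 | 25.0% | 25.3% |

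Coverage of the nominal 95% CI is 100% minus the type I error. If 450 students fell in only 20 classes (22.5 each), ICC 0.10 would give DE 3.15 and about 27%. At ICC 0 the simulated rate is 5%.

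**Schools also differing in change.** With a school component of 0.02 added to class components of 0.02 / 0.05 / 0.10 and 15 per class, simulated rejection rates are:
- paired t-test: 21% / 25% / 30%
- t-test on 24 class means: 12% / 10% / 9%
- t-test on six school means: 5% throughout

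With 20 per class, the paired t-test rejects 26% / 30% / 35% and the class-mean test 13% / 11% / 9%.

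**Regression slopes.** For a predictor with its own class ICC, the variance inflation is about 1 + (m − 1)·ICC_y·ICC_x. At 0.05 and 0.05 with m = 15 this is 1.035 (type I about 5.4%). At 0.10 and 0.10 with m = 20 it is 1.19 (about 7.2%). A predictor constant within class has ICC_x = 1, so the full DE returns.

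**Sample size.** The smallest effective N in the table is 150. With the school component of 0.02, class component 0.10 and m = 15 (60 per school), DE = 1 + 14 × 0.12 + 45 × 0.02 = 3.58 and effective N = 360/3.58 ≈ 101. All exceed 77. At effective N 166, power for f² = 0.15 with three predictors is about 0.99.

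**The case against.** The strongest reply is about what is being estimated. Schools were conveniently selected, teachers are first-come, and Section 2.2 disclaims a representative sample. For the mean change in these particular classes, the student-level paired t-test is valid. That is correct, and it is why the point is limited to inference beyond them. It does not dispose of the point, because the article wants its results to inform wider use, in Greece and elsewhere.

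Second, the size rests on an ICC that the article does not supply. Common materials, common training and Master Trainers overseeing every session may hold it down. This stands: the figures are illustrative, and at ICC 0.01 the error is only about 7%.

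Third, the study is an exploratory single-arm pilot, and without a control group a pre-post change cannot be attributed to the program whatever its standard error. That lowers the severity. It does not excuse the intervals, since Section 2.7 makes them the evidence.

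A reader might infer two stronger claims, and neither is supported. One is that every planned regression shares this inflation. Section 2.6 names individual attitudes and perceptions as the key predictors, and slopes on these are hardly affected. The other is that the study is too small. The expected 450 to 480 students leave effective N well above 77.

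**Conclusion.** The concern holds for the pre-post mean change. The named method gives CIs that are too narrow for inference beyond the participating classes if change varies by class or teacher, which the article's own limitations make plausible. On the assumed ICC range of 0.01 to 0.10, with about 24 classes of 15 to 20 pairs, correct intervals are about 1.07 to 1.70 times as wide, and type I error is about 7% to 25% (about 27% with 22.5 per class). It is higher again if schools differ in change.

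The same inflation reaches regression intercepts and any class-, teacher- or school-level predictor. Slopes on individual-level predictors stay at about 5% to 7%. The sample size needs no increase. Severity: should-fix.

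**What to change.** 1. Make sure that class and school identifiers are captured with both student questionnaires. They are hard to recover later.
2. In Section 2.7, replace the student-level paired t-test with a t-test on class mean changes (about 23 df). Alternatively, fit a two-time-point mixed model with random student and class intercepts, a random class-by-time effect and small-sample degrees of freedom. A class intercept alone does not correct the standard error of the time effect.
3. Report the t-test on six school mean changes (5 df) prominently beside it. A fixed school main effect is no substitute: in a trial fit of the mixed model to simulated data, the standard error of time was 0.0851 with and without it.
4. In the regressions, use a class random effect, or cluster-robust errors with a small-sample correction.
5. Report the ICC of the change score.

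The cost is a change of wording, two identifiers and wider intervals. Before any change in the standard error, the critical value alone widens the interval by 2.069/1.960 = 1.06 at class level and 2.571/1.960 = 1.31 at school level.
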